# SUMMARY

**Rationale:** Surgical procedures for gastrointestinal oncology intervention are inevitably highly variable amongst surgeons and centers. Although acceptable to a degree, a substantial proportion of this variability has a potential relevance for both short term clinical outcomes and long term survival. For patients with right-sided colon cancer, a laparoscopic right hemicolectomy (LRHC) is the surgical procedure to remove the cancer and locoregional lymph nodes. This surgical technique has evolved during the last decade with the introduction of the intracorporeal anastomosis, the Pfannenstiel extraction and the complete mesocolic excision (CME). The latter is a dissection technique in embryological planes with a central vascular ligation of the segmental branches at its origin, resulting in an optimal lymphadenectomy. Given the insights from recent studies showing a positive association between the quality of surgery and relevant clinical outcomes, there is a great need to reduce the interinstitutional and intersurgeon variability and to implement an optimized and standardized surgical technique for right-sided colon cancer in the Netherlands to improve short- and long-term clinical and oncological outcomes. This kind of implementation needs a consensus of the key elements of the procedure and a formative quality assessment of LRHC. Detailed objective assessment of the LRHC is currently not performed in clinical practice nor in surgical training. Quality assessment of LRHC has great potential to improve surgical training and furthermore, implementation of a standardized technique will ultimately lead to better quality of care for patients suffering from right-sided colon cancer.

**Objective**: The main objective of this study is to improve surgical outcomes for patients with right-sided colon cancer by a prospective sequential interventional cohort study that aims to standardize the surgical technique with subsequent controlled implementation after standardized review of the current practice in a nationwide multicenter setting.

**Study design:** Prospective interventional sequential cohort study.

**Study population:** Patients with planned laparoscopic or robot-assisted (extended) right hemicolectomy for colon cancer of the caecum, ascending colon or hepatic flexure.

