## Other study objectives

- To evaluate current practice and variations in technique for laparoscopic right hemicolectomy in the Netherlands.

- To give an overview of the vascular anatomical variations pertinent to laparoscopic right hemicolectomy.

- To evaluate the association of each variation performed in laparoscopic right hemicolectomy with the short- and long-term clinical and oncological outcomes.

- To reach consensus for a standardized step wise technique for laparoscopic right hemicolectomy using the most recent insights in optimized colon cancer surgery from literature and the results from the assessment during the first phase of the study, according to the Delphi method.

- Development and validation of a Competency Assessment Tool (CAT) for the standardized right hemicolectomy using surgical full-length videos of the laparoscopic right hemicolectomy procedures and the steps as identified in the Delphi method.

- To train and implement the standardized surgical technique in centers in the Netherlands for patients with right-sided colon cancer.

- To evaluate the short- and long-term clinical and oncological outcomes of the cohort after training and compare these with the cohort before training, implementation and proctoring of the standardized technique.

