## Hypothesis

The primary hypothesis of this study is that the implemented and standardized laparoscopic surgical technique for right-sided colon cancer will be safe without an increase in the 90 days postoperative morbidity (non-inferiority design).

The second hypothesis is that the quality of surgery, objectively assessed by competency assessment, is an important determinant for long-term clinical patient outcomes.

The clinical outcomes of the surgical technique to treat right-sided colon cancer will be improved by safely implementing a standardized method according to the latest evidence. Improvements in outcome measures that reflect the oncological quality of surgery, such as validated assessment of plane of dissection and vascular ligation, grading of the resection specimen, total lymph node count and number of resected positive lymph nodes and completeness of mesocolic excision based on postoperative CT imaging are expected. Eventually, it is hypothesized that the surrogate oncological endpoints will translate in reduction of local and distant recurrences and improved 5-year overall survival (OS) and 3-year disease free survival (DFS).

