# STUDY DESIGN

The design of this trial is a multicenter prospective interventional sequential cohort study with a transition period in which implementation of the standardized technique is performed in the same centers after education and hands on training. Proctoring of the new technique will be provided during implementation. The second data evaluation of the clinical and oncological outcomes of the consecutive patient group will be collected in the group of patients after proctoring is finished, the so called consolidation phase. This study is primarily designed as a non-inferiority trial, based on short-term postoperative complications, with the aim of ultimate improvement of long-term oncological outcome. The accrual of both the control patients and the patients after implementation will be within the national Prospective Dutch ColoRectal Cancer cohort (PLCRC) with additional video analysis and image collection with additional informed consent. The primary endpoint is safety during implementation of a new technique. This is measured by 90-day morbidity with the Clavien-Dindo classification [15]. The assumption is that the perioperative morbidity (26% 30-day overall postoperative complication rate; as earlier published based on the DCRA database [16]) will not be increased by implementation of the new standardized technique with a non-inferiority margin of 7%, therefore not exceeding 33%.

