## Study procedures

First the variability of surgical techniques amongst surgeons and centers for right-sided colon cancer will be evaluated by a 4 months period (possibility to extend until maximum of 6 months) prospective inclusion of 365 patients and evaluating preoperative CT imaging, full length surgical video and clinicopathological outcomes, as well as the CT imaging one year post-operatively as routine part of oncological follow-up.

Second, a Delphi method amongst participating colorectal surgeons will be applied after the 4 months period (possibility to extend until maximum of 6 months) of video collection, to establish a detailed standardized technique for laparoscopic right hemicolectomy for colon cancer. This technique will include essential elements that can potentially improve outcomes such as approach, number and positioning of trocars, plane of retroperitoneal dissection, level of vascular ligation with extent of vertical lymphadenectomy, technique for constructing the anastomosis and preferred extraction site.

Third, the standardized technique will be taught during hands-on surgical training.

Fourth, the new technique will be implemented in a controlled fashion with proctoring in the same centers, with another 4 months period (possibility to extend until maximum of 6 months) of prospective inclusion of 365 patients.

Finally, a third consecutive group of patients will be included to consolidate the standardized technique after the learning curve. The same preoperative CT imaging, full length surgical videos and clinicopathological outcomes as well as the CT imaging one year post surgery will be collected and analyzed, in order to be able to compare the performance with the pre-implementation period. Again, 365 patients will be prospectively included in a 4 months period (possibility to extend until maximum of 6 months).

Schematic five step approach:

[figure not shown]

1. **Control cohort phase**: Prospective mapping of current practice with surgical variations in laparoscopic right hemicolectomy (total duration of inclusion 4 months, possibility to extend until maximum of 6 months). N=40+ centers; N=365 videos
   1. METC approval for the use of anonymized videos of a laparoscopic procedure and collection of corresponding clinical outcomes.
   2. Approaching hospitals for participation (high volume centers (50+ colon cancers).

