# STATISTICAL ANALYSIS

The clinical outcomes will be categorical or dichotomous outcomes and will be presented as absolute numbers and percentages. The chi-square test will be used for comparing categorical data among patient groups. Descriptive outcomes will be reported as median with interquartile range (IQR) or mean with standard deviation (SD) and in accordance to their distribution the Mann-Whitney-U test is used to evaluate intergroup variation.

Oncological outcome will be determined using Kaplan-Meier analyses, with comparison of relevant patient groups using the log-rank test. Predictors of main outcome parameters will be determined by selecting relevant variables based on expected association with subsequent univariable analysis. Besides stratified comparisons as described above, multivariable analysis will be performed to determine independent association of factors with a specific outcome parameter using logistic and Cox regression analyses. A p-value <0.05 will be considered to be statistically significant. All analyses will be performed with IBM SPSS statistics, version 23.00 (IBM Corp Amonk, NY, United States).

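### Section 10 analyses patients as independent, so standard errors for the technique and competency associations would be too small; the primary contrast is only modestly affected

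*Protocol*

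**What the plan says.** The Summary opens from the premise that "Surgical procedures for gastrointestinal oncology intervention are inevitably highly variable amongst surgeons and centers". Section 8.2 makes mapping that variability the first step of the study and gives the scale of each cohort as "N=40+ centers; N=365 videos". The implementation and consolidation cohorts come from the same centres as the control cohort.

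Two aims depend on that variability. Section 4.2 lists as an objective: "To evaluate the association of each variation performed in laparoscopic right hemicolectomy with the short- and long-term clinical and oncological outcomes". Section 4.3 states as second hypothesis that "the quality of surgery, objectively assessed by competency assessment, is an important determinant for long-term clinical patient outcomes".

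Section 10 then fixes the methods. For proportions: "The chi-square test will be used for comparing categorical data among patient groups". The Mann-Whitney U test is named for continuous measures and the log-rank test for survival. For the associations, "multivariable analysis will be performed to determine independent association of factors with a specific outcome parameter using logistic and Cox regression analyses". The significance level is 0.05. Centre and surgeon do not appear in the section in any role. It mentions stratified comparisons as already described, but nothing before that mention names centre or surgeon as a stratum.

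The primary comparison is sized from a "26% 30-day overall postoperative complication rate" and a "non-inferiority margin of 7%, therefore not exceeding 33" per cent, with 365 control patients against 730 from the two later cohorts (section 6.4).

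**The concern.** If technique and quality are partly habits of a surgeon or a centre, and outcome also differs between centres, patients from one centre carry overlapping information. A method that counts them as independent then overstates precision.

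This matters most for the section 4.2 objective and the section 4.3 hypothesis. There the exposure itself clusters, so a chance difference between a few centres can look like an effect of a technique or of a competency score. Section 4.2 also says that first-phase results, together with the literature, inform the Delphi consensus. Over-read short-term associations could therefore influence the technique that is later taught.

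The primary before-after contrast is different. Each centre contributes to both sides, so stable centre differences largely cancel. What remains is how unequally centres change between phases, which the planned chi-square test does not take into account.

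**Working it through.** **Inputs from the protocol.** Control rate 26%, margin 7 points, one-sided 5%, 80% power, true difference zero, 365 v 730, at least 40 centres, same centres in all phases.

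**Inputs assumed.** The protocol gives no ICC, no correlation of centre effects between phases, and no centre sizes. I use 40 equal centres, an outcome ICC of 0.02 to 0.05 and a between-period correlation of 1.0 (stable) to 0.5. Patients per centre: 365/40 = 9.125 per cohort and 1095/40 = 27.375 over three cohorts.

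**1. The plan's own figure.** For a 1:2 allocation with independent binomial variance:

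n(control) = (1.645 + 0.842)² × 0.26 × 0.74 × (1 + 1/2) / 0.07² = 364.1, rounded up to 365.

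This gives 365 + 730 = 1095 and a power of 80.1%. The stated size reproduces exactly with no design effect, so it contains no allowance for clustering.

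**2. Exposure constant within centre, one cohort.** Design effect = 1 + (m − 1) × ICC with m = 9.125. True error of a nominal two-sided 5% test = 2 × P(Z > 1.96/√design effect).

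- ICC 0.02: 1 + 8.125 × 0.02 = 1.16; error 6.9%.
- ICC 0.05: 1 + 8.125 × 0.05 = 1.41; error 9.8%.

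These are upper ends for this ICC range, because they suppose that all patients of a centre share the same exposure.

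**3. Partly clustered exposure, all three cohorts pooled.** If the exposure has its own within-centre correlation, assumed here to be 0.5, the design effect is approximately 1 + (m − 1) × ICC × 0.5 with m = 27.375.

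- ICC 0.02: 1 + 26.375 × 0.02 × 0.5 = 1.26; error 8.1%.
- ICC 0.05: 1 + 26.375 × 0.05 × 0.5 = 1.66; error 12.8%.

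**4. Primary contrast, 365 v 730.** The three cohorts are three separate inclusion periods with m = 9.125 patients per centre in each, and the experimental side is the mean of two of them. Let r be the between-period correlation of centre effects. The ratio of true to naive variance reduces to (1 − ICC) + m × ICC × (1 − r).

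- ICC 0.02, r = 1: 0.98.
- ICC 0.02, r = 0.5: 0.98 + 9.125 × 0.02 × 0.5 = 1.07.
- ICC 0.05, r = 1: 0.95.
- ICC 0.05, r = 0.5: 0.95 + 9.125 × 0.05 × 0.5 = 1.18.

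True one-sided error = P(Z < −1.645/√ratio): 4.6% at 0.95 and 6.5% at 1.18.

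The naive standard error is √(0.26 × 0.74 × (1/365 + 1/730)) = 0.0281. Power with the correct standard error = P(Z < 0.07/(0.0281 × √ratio) − 1.645): 82% at 0.95 and 74% at 1.18.

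**The case against.** **This is matter for the analysis plan.** Random effects, robust variances and frailty terms are often left to that document, which is not shown. Logistic and Cox regression do not exclude a centre term, and section 10 leaves the choice of covariates open. This stands in part: the regression models could be completed correctly later. But the protocol does more than stay silent. It names chi-square, Mann-Whitney and log-rank tests that assume independent patients, names no cluster term for the models, and sizes the trial on independent variance, against its own premise.

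**Exposure is not a pure centre trait.** Competency is rated from individual videos, and the Summary places the variation among surgeons as well as centres. This stands, and it is why the single-cohort figures are upper ends. The number of surgeons is not given, so clustering at that level cannot be sized.

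**A much larger error over all 1095 patients.** A reader might apply the full design effect to the pooled data: 1 + 26.375 × 0.02 = 1.53 to 1 + 26.375 × 0.05 = 2.32, or 11.3% to 19.8% error. The documents do not support this. It needs an exposure that stays constant within a centre through all three phases, and the intervention exists to change technique within centres. The partly clustered range of about 8% to 13% is the defensible one, and only for exposures that remain centre-specific.

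**A biased primary test.** A reader might also infer that the non-inferiority test is clearly too liberal. It need not be: with stable centre effects it is slightly conservative. Treating implementation and consolidation as one period with a single shared centre effect would raise the worst variance ratio to about 1.25, but section 8.2 makes them separate inclusion periods, which gives 1.18.

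**The route to the Delphi consensus is narrow.** The five-step scheme in section 8.2 names only literature and expert opinion as the source of the crucial steps. The Delphi phase follows directly after the first 4 to 6 months of collection, so three- and five-year outcomes cannot reach it. At most, short-term associations could.

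**Conclusion.** Wrong as written, with a limited and partly uncertain size. For the secondary technique-outcome and competency-outcome analyses, methods that ignore centre and surgeon give standard errors that are too small whenever both exposure and outcome cluster, which is what the protocol itself supposes. With 40 equal centres and an ICC of 0.02 to 0.05, the nominal 5% error becomes at most about 6.9% to 9.8% in one cohort. It is about 8% to 13% in pooled analyses of exposures with an assumed within-centre correlation of 0.5.

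For the primary contrast the direction is unknown and the effect modest: variance ratio about 0.95 to 1.18 over the assumed range. This does not overturn the non-inferiority design, but the error rate of a safety claim should not depend on an unexamined assumption.

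All these sizes rest on assumed correlations and equal centre sizes. That section 10 and the sample size make no allowance for clustering does not.

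**What to change.** Amend section 10, or fix in the analysis plan with a reference from section 10, as follows:

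- **Technique and competency associations:** mixed-effects or GEE logistic models for binary outcomes, and Cox models with centre-clustered variance or shared frailty for survival. Nest surgeon within centre where the surgeon is recorded.
- **Primary comparison:** estimate the risk difference and its 90% confidence interval with centre-clustered robust variance, or from a model with phase, centre and centre-by-phase effects, in place of the plain chi-square test.
- **Reporting:** give the estimated ICC.

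The cost is wording, slightly more analysis work, and possibly software other than the named SPSS version for the clustered or frailty Cox models. Intervals for centre-level exposures will be wider, which reflects the information actually available. No extra patients are needed.

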# ETHICAL CONSIDERATIONS

## Regulation statement

This study will be conducted according to the principles of the Declaration of Helsinki (Fortaleza, Brasil, October 2013) and in accordance with the Medical Research Involving Human Subjects Act (WMO) and other guidelines, regulations and acts.

## Recruitment and consent

Suitable patients will be approached for entry into the trial at the first outpatient visit at the surgery department after diagnosis of colon cancer of the caecum, ascending colon or hepatic flexure has been made. The rationale for the trial is explained to the patient. A written patient information sheet is provided and patients will be given the opportunity to ask questions. The informed consent will be obtained before the operation. Written informed consent is taken by surgeons, surgical registrars or trained research nurses. When consent has been obtained, the original form is kept in the trial file and a copy is given to the patient. Baseline data as well as baseline questionnaires are collected.

## Objection by minors or incapacitated subjects (if applicable)

Minors and legally incompetent adults are excluded from the trial.

## Benefits and risks assessment, group relatedness

Patients included in the first period (prospective mapping of surgical variations) do not directly benefit from participation in this study. Patients included in the second period (implementation of standardized laparoscopic right hemicolectomy) might benefit from the implementation and could have less postoperative complications.

## Compensation for injury

The sponsor/investigator has a liability insurance which is in accordance with article 7 of the WMO.

The sponsor (also) has an insurance which is in accordance with the legal requirements in the Netherlands (Article 7 WMO). This insurance provides cover for damage to research subjects through injury or death caused by the study.

The insurance applies to the damage that becomes apparent during the study or within 4 years after the end of the study.

## Incentives (if applicable)

Enrolled patients will not receive any special interventions, compensation or treatment through participation in this trial.

# ADMINISTRATIVE ASPECTS, MONITORING AND PUBLICATION

## Handling and storage of data and documents

Every included patient will be assigned a three digit study number. Communication occurs only with this number. The full name and date of birth of the patient will only be recorded on the informed consent form.

A study coordinator coordinates the study, monitors patient inclusion and protocol steps, data collection, data entry, preparation and performs analyses and will report the data. Continuous data monitoring and data collection on a CRF will guarantee complete and real-time prospective recording of data. Data will be collected and stored at the VUmc in a separate, closed room.

There is a collaboration with FormsVision, a privately owned business delivering clinical IT solutions to the academic community and the pharmaceutical industry, that can build the digital platform (<https://www.aleaclinical.eu/>) to facilitate assessment of high volume full length videos of surgical procedures with clinical safety requirements concerning privacy regulations. The design allows secure online worldwide access to upload unlimited data 10+ GB full length video and allows automatic consignments to reviewers by email and link towards reviewer account with the ability to assess the quality of surgery. The digital platform is also designed to add all relevant clinical data related to clinical outcomes.

## Amendments

Amendments are changes made to the research after a favourable opinion by the accredited METC has been given. All amendments will be notified to the METC that gave a favourable opinion.

All substantial amendments will be notified to the METC and to the competent authority.

Non-substantial amendments will not be notified to the accredited METC and the competent authority, but will be recorded and filed by the sponsor.

A ‘substantial amendment’ is defined as an amendment to the terms of the METC application, or to the protocol or any other supporting documentation, that is likely to affect to a significant degree:

- The safety or physical or mental integrity of the subjects of the trial;
- The scientific value of the trial;
- The conduct or management of the trial; or
- The quality or safety of any intervention used in the trial.

## Annual progress report

The sponsor/investigator will submit a summary of the progress of the trial to the accredited METC once a year. Information will be provided on the date of inclusion of the first subject, numbers of subjects included and numbers of subjects that have completed the trial, serious adverse events/ serious adverse reactions, other problems, and amendments.

